### Monitoring for adverse events

A formal Data Monitoring Committee (DMC) constituted by the New Zealand Health Research Council Data Monitoring Core Committee will monitor safety and trial conduct according to the terms of its charter. An independent study statistician and data manager will generate both the open and closed Reports for the DMC, and have no connection to the clinical aspects of the trial. Because of power considerations and the fact that safety of low dialysate [Na+] was demonstrated in the pilot study, no interim analyses are planned and no stopping rule based on statistical significance of efficacy data, frequentist or Bayesian, has been set. However, safety reports will be made and reviewed by the DMC on a 6 monthly basis.

### Power calculation

Power calculations are based on the primary outcome measure of LVMI. The SoLID trial assumes a baseline mean (standard deviation, SD) LVMI of 110 (40) g/m2, based on published data in HD populations using cardiac MRI [33,174,175]. The trial assumes a 12 month follow-up LVMI of 95 (35) g/m2 in the low dialysate [Na+] group based on the change in LVMI observed over 6 months in clinical trials of frequent or nocturnal HD [27,34,35]. Correlation between baseline and 12-moth follow-up measurements of LVMI in the SoLID trial is assumed to be 0.75 based on private communication from the [name] group (private communication [name] 8/2/2011): in a cohort of 59 patients of their patients with repeated measures of LVMI at least 6 months apart (using cardiac MRI), correlation was 0.87 (p < 0.001) with normally distributed data [33,174,175]. Modelling these data using repeated-measures analysis of covariance (ANCOVA), and allowing for 25% for drop outs, 59 participants will be enrolled in each arm (power 0.8, alpha 0.05). The SoLID trial will therefore enrol 118 trial participants over the 6 participating sites in NZ.

### Analysis populations

For analysis of data, we define Intention to Treat (ITT) and Per Protocol (PP) populations. The ITT population consists of all randomised participants who have at least one baseline measurement, and is the primary population of interest. All randomised participants will be analysed in the group they were allocated to, even if they do not receive the allocated treatment, do not commence treatment, change dialysis modality, are lost to follow-up, or die thereby preserving the intention-to-treat framework. In particular, titration failures will remain within the ITT population as participants.

The PP population consists of participants that fulfil criteria for the ITT population, have complete primary endpoint measurements and do not present any major protocol violations during the study. The following describes the major protocol deviations that will exclude patients from the PP population (minor deviations will not do so): eligibility violation; absence of any efficacy data, titration failure; other major violations will be identified by the DMC of the trial during the study and/or during the data review process. The list of all protocol deviations will be reviewed by the DMC who will determine the degree of the violation (i.e. major versus minor). All protocol deviations considered as minor will not lead to excluding patients from the PP population for analysis.

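### The DMC, which receives closed reports, grades every protocol deviation under an open-ended category and so decides who enters the secondary per-protocol analysis of LVMI

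*Protocol article*

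**What the plan says.** Four statements in the protocol article bear on this.

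- **Who enters the per-protocol (PP) set** (Analysis populations). Participants must meet the intention-to-treat (ITT) criteria and "have complete primary endpoint measurements and do not present any major protocol violations during the study".
- **What counts as major** (same section). Three categories are named: "eligibility violation; absence of any efficacy data, titration failure". A fourth is left open: "other major violations will be identified by the DMC of the trial during the study and/or during the data review process".
- **Who grades** (same section). "The list of all protocol deviations will be reviewed by the DMC who will determine the degree of the violation (i.e. major versus minor". Deviations graded minor do not exclude anyone.
- **What the committee receives** (Monitoring for adverse events). "An independent study statistician and data manager will generate both the open and closed Reports for the DMC". Also, "safety reports will be made and reviewed by the DMC on a 6 monthly basis", and "no interim analyses are planned and no stopping rule based on statistical significance of efficacy data, frequentist or Bayesian, has been set".

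Table 2 lists the PP analysis of the primary endpoint among the secondary analyses. The ITT population "is the primary population of interest".

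**The concern.** Exclusion from a PP set is selection after randomisation. It is tolerable when the rule is fixed in advance or applied by people who know neither arm nor outcome. Here neither condition is stated. The fourth category has no criteria. It can be filled during data review, when outcome data may already exist. The grader is the one body for which closed reports are produced.

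The grading sentence covers all deviations, so it is also unclear whether the three named categories exclude a participant automatically or are themselves open to regrading.

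Allocation matters here even without LVMI results. Treatment is open after randomisation (Blinding), and masked image reading is the safeguard for the primary endpoint. A PP set chosen by people who know the arm works around that safeguard for this analysis. By-arm blood pressure or hypotension data would also be informative, since blood pressure is part of the mechanism under study. Deviations may themselves point to the arm: from the median New Zealand setting of 139 mM (Interventions), reaching 135 mM is a 4 mM change and reaching 140 mM is a 1 mM change.

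**Working it through.** **Chain of responsibility.** Set side by side, the sections give this sequence: closed reports go to the DMC; the DMC grades all deviations and may add major ones; a major grade removes the participant from the PP set; the PP set is used for a secondary analysis of LVMI. Each link is stated. The article does not say what the closed reports contain, whether the deviation listing is masked, or whether grading is finished before LVMI is linked to allocation.

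**The plan's own figure.** Inputs from Power calculation: SD 40 at baseline and 35 at follow-up, correlation 0.75, follow-up mean 95 in the low-sodium arm, power 0.8, alpha 0.05 (two-sided under Statistical analysis), 25% drop-out. Assumption: the control arm stays at 110, so the difference is 15 g/m2; the article gives no control follow-up mean.

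- Pooled SD = √((40² + 35²)/2) = √(2825/2) = 37.58
- Residual SD = 37.58 × √(1 − 0.75²) = 37.58 × √0.4375 = 24.86
- n per arm = 2 × (24.86 × (1.960 + 0.842)/15)² = 43.1, so 44
- 44/0.75 = 58.7, so 59 per arm, as stated

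**Standard error of the adjusted contrast at 44 per arm.** √(2825 × 0.4375/44) = 5.30 g/m2.

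**Illustration of size.** Assume that 4 of 44 low-sodium participants are graded major, all in that arm, and that their follow-up LVMI averages 30 g/m2 above the other 40. The planned ANCOVA adjusts for baseline (Primary outcome), so the part of the excess that baseline predicts must come out first.

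- Expected baseline-adjusted excess = 30 × (1 − 0.75²) = 30 × 0.4375 = 13.1 g/m2
- Shift in the adjusted contrast when the 4 are removed = 4 × 13.1/44 = 1.19 g/m2
- Relative to the difference: 1.19/15 = 8%
- Relative to the standard error: 1.19/5.30 = 0.22

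**Range under other assumptions.** Suppose the k participants removed lie one residual SD (24.86) above the mean of all 44. The shift is k × 24.86/(44 − k).

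- k = 2: 49.72/42 = 1.2 g/m2
- k = 5: 124.3/39 = 3.2 g/m2

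The article gives no expected deviation rate, so none of these counts can be checked against it.

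**The case against.** The strongest defence has four parts.

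- **The DMC is a reasonable grader in an open trial.** It is constituted externally by the funder's core committee, its remit already includes trial conduct, and investigators and coordinators know the allocation anyway. This stands in part: moving the task to site staff would be no improvement. It does not justify giving the task to a body that receives closed reports when masked graders are possible.
- **Most of the PP definition is fixed.** Complete primary endpoint measurements and three named categories do most of the work, so discretion falls mainly on the remainder. This stands, subject to the ambiguity over whether the named categories can be regraded.
- **Safeguards may sit in the charter or SAP.** They may, and silence on masking alone would be no finding. But the article positively assigns the grading to the DMC, so a SAP that moved it would contradict the article.
- **Only a secondary analysis is exposed.** This stands.

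Two stronger readings are tempting. A reader might infer that the DMC would choose exclusions knowing the emerging LVMI results by arm. The article does not support that: no interim analysis is planned, the six-monthly reports are described as safety reports, and LVMI is measured only at baseline and 12 months and read by blinded analysts. That closed reports show data by arm is the usual meaning of the term, not something the article states.

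A reader might also take the raw shift, 4 × 30/44 = 2.7 g/m2, as the effect on the analysis (18% of 15, or 0.51 of 5.30). That sets an unadjusted excess against a baseline-adjusted standard error. It would be right only if baseline LVMI explained none of the excess, contrary to the planned correlation of 0.75.

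**Conclusion.** The point holds in a limited form. A body that may know allocation and by-arm safety data has open-ended discretion, lasting into data review, over membership of the PP set. The exposure is confined to the PP analysis of LVMI; the primary ITT estimate, the sample size and the power calculation are untouched. The article does not state that the PP result will be used to support the primary one, and its position in Table 2 implies no declared ranking.

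The illustrated shift is about 1.2 g/m2, and up to about 3 g/m2 if 5 participants were removed at one residual SD. These figures rest on assumed counts, an assumed excess, all removals falling in one arm, and a control mean that stays at 110. They show that the effect could be noticeable without dominating the result; they do not predict it. This is a cheap improvement worth making, not a threat to the trial's main conclusion.

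**What to change.** - Close the list of major deviations in advance, and state that eligibility violation, absence of efficacy data and titration failure exclude automatically from the PP set.
- Have any remaining cases graded by people with no access to closed reports or LVMI who are not site staff aware of allocation, for example blinded data-management or statistical staff. The statistician and data manager who prepare the closed reports would not qualify.
- Give them listings stripped of allocation, dialysate level and outcome data, and require sign-off before LVMI is linked to allocation.
- Leave safety and trial conduct with the DMC.

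The cost is a wording change in the protocol, the SAP and the DMC charter, plus some redaction work. Masking will be imperfect where the nature of a deviation reveals the dialysate level. Sample size, visits and data collection do not change.

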### Statistical analysis

Primary and secondary subgroup and non-subgroup analyses are provided in Table 2. For statistical analyses, we define predictors, related to outcome and unrelated to the allocation; potential confounders, related to outcome and imbalanced by chance across the treatment arms; and potential effect modifiers, that may moderate the treatment arm effect. The former two are hereafter identified as potential covariates.

**Table 2 T2:** Primary and secondary analyses

**Analyses**	**Population**	**Subgroup**	**Endpoints**	**Framework**
Primary	ITT	None	Primary	Univariate
Secondary	PP	None	Primary	Univariate
	ITT	None	Secondary	Univariate
	ITT	None	Secondary	Multivariate
	ITT	Baseline LVMI subgroups (observed median LVMI as the level boundary)	Primary	Univariate
	ITT	Baseline LVMI subgroups (observed median LVMI as the level boundary)	Time-averaged blood pressure over months 3, 6, 9 and 12 (intra-dialytic, inter-dialytic), % maximum recommended daily dose of antihypertensives	Multivariate, accounting for subgroup effect and treatment-subgroup interaction, FDR control to account for multiplicity
	ITT	Baseline intra-dialytic and inter-dialytic blood pressure subgroups (observed mean blood pressure as the level boundary)	Primary	Univariate, accounting for subgroup effect and treatment-subgroup interaction, and three-way interaction
	ITT	Baseline intra-dialytic and inter-dialytic blood pressure subgroups (observed mean blood pressure as the level boundary)	Time-averaged blood pressure over months 3, 6, 9 and 12 (intra-dialytic, inter-dialytic), % max recommended daily dose of antihypertensives	Univariate, accounting for subgroup effect and treatment-subgroup interaction, and three-way interaction, FDR control to account for multiplicity
	ITT	Baseline pre-dialysis plasma Na+ ionic activity subgroups (observed median plasma Na+ ionic activity as the level boundary)	Primary	Univariate, accounting for subgroup effect and treatment-subgroup interaction
	ITT	Baseline pre-dialysis plasma Na+ iIonic activity subgroups (observed median plasma Na+ ionic activity as the level boundary)	Time-averaged blood pressure over months 3, 6, 9 and 12 (intra-dialytic, inter-dialytic), % maximum recommended daily dose of antihypertensives	Univariate, accounting for subgroup effect and treatment-subgroup interaction, and three-way interaction, FDR control to account for multiplicity
Tolerability	ITT	None	Hypotension event counts	Multivariate, mixed effects, allowing for treatment time interaction

Abbreviations: *PP* per protocol, *ITT* intention to treat, *LVMI* left ventricular mass index, *FDR* False Discovery Rate.

All tests of significance of hypotheses concerning treatment effect parameters will be carried out using a level of significance of 5% and two-sided alternatives. The significance threshold of potential covariates will be set at 10%, to promote unbiased and conservative inference. All estimates will be produced as point estimates and as 95% confidence intervals. Unless otherwise noted, model selection when required will be performed using backward selection from the largest model dictated by the situation. Per comparison error rate (PCER) control will be used in all analyses, with the exception of some subgroup analyses where False Discovery Rate (FDR) control will be implemented.

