### Randomisation

Once baseline assessments have been completed and 28 days have elapsed since enrolment onto the trial, randomisation will be performed using a phone based interactive voice response system (IVRS) from the National (Australia) Health Medical Research Council (NHMRC), Clinical Trials Centre (CTC) Sydney, Australia. Participants will be randomised in computer generated blocks of random size (undisclosed), blinded to investigators, and stratified by a) treating centre, and b) whether they receive conventional (≤18 hours/week) or extended-hour (>18 hours/week) HD.

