### Primary outcome

For LVMI, we will undertake univariate (single outcome) endpoint analysis. Score residuals will be checked for approximate normality and an appropriate normalising transformation applied to the endpoint data if appropriate and possible. We will use analysis of covariance (ANCOVA) to estimate the treatment effect, adjusting for baseline and potentially adjusting for covariates, if applicable. The resulting treatment contrast will be reported as a point estimate and as a 95% confidence interval.

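### The primary ANCOVA may choose its covariates from trial data at a 10% threshold, which the article calls conservative; with backward selection the type I error can instead exceed 5%

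*Protocol article*

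**What the plan says.** The Primary outcome subsection analyses 12-month LVMI by ANCOVA, "adjusting for baseline and potentially adjusting for covariates, if applicable". Only baseline LVMI is certain to be in the model.

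The Statistical analysis section says where other covariates come from. One group is predictors of outcome. The other is "potential confounders, related to outcome and imbalanced by chance across the treatment arms". After Table 2 it sets the criterion, "The significance threshold of potential covariates will be set at 10%, to promote unbiased and conservative inference", and the default procedure: unless otherwise noted, "model selection when required will be performed using backward selection from the largest model dictated by the situation". The Primary outcome subsection notes no other procedure.

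Tests of treatment effect "will be carried out using a level of significance of 5% and two-sided alternatives", and estimates carry 95% intervals. No sentence adjusts the test or the interval for covariate selection.

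Under Randomisation, allocation is "stratified by a) treating centre, and b) whether they receive conventional (≤18 hours/week) or extended-hour (>18 hours/week) HD". The analysis sections neither put these two factors in the primary model nor leave them out.

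**The concern.** Chance imbalance is visible only after randomisation, and association with outcome only once follow-up LVMI is known. The covariate set of the one primary test is therefore open until the outcome data are in hand.

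Backward selection keeps the covariates that happen to explain the outcome in this sample. The ordinary ANCOVA output treats the surviving model as if it had been chosen in advance. It charges degrees of freedom only for the survivors, and its residual variance is too small. The p-value and interval can then be too optimistic, which is the opposite of what the article claims for its rule. At stake are the nominal 5% level of the primary test and the reader's trust that the model was fixed before the result was known.

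**Working it through.** **1. The plan's own sample size.** The Power calculation section states: "The SoLID trial assumes a baseline mean (standard deviation, SD) LVMI of 110 (40) g/m2". It gives 95 (35) at 12 months in the low-sodium arm, correlation 0.75, power 0.8, alpha 0.05 and 25% dropout. It does not state the 12-month control value; I take it as unchanged at 110 (40), so the difference is 15.

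- Root-mean-square SD: √((40² + 35²)/2) = √1412.5 = 37.6.
- Residual SD after baseline: 37.6 × √(1 − 0.75²) = 24.9.
- n per arm: 2 × (1.96 + 0.84)² × 24.9² / 15² ≈ 43.1, rounded up to 44.
- With dropout: 44 / 0.75 = 58.7, rounded up to 59 per arm, 118 in all.

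This matches the article. The primary analysis is thus planned on about 2 × 44 = 88 completers.

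**2. Type I error by selection rule.** Simulation set-up: 88 completers, 1:1 allocation, no treatment effect, arm and baseline always in the model, r = 0.75, independent normal covariates, 10,000 trials per row. The Monte Carlo standard error is √(0.05 × 0.95 / 10,000) ≈ 0.2 points. My assumptions are the number of candidates, how many are prognostic (coefficient 0.2 per SD) and a 10% cut-off for imbalance. Entries are % rejected at a nominal 5%.

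| Candidates (prognostic) | Baseline only | All candidates, fixed | Backward at 10% | Outcome-related and imbalanced |
|---|---|---|---|---|
| 5 (0) | 4.99 | 4.81 | 5.47 | 4.86 |
| 5 (2) | 4.89 | 5.00 | 5.46 | 4.36 |
| 10 (0) | 5.08 | 5.04 | 5.96 | 4.93 |
| 10 (3) | 4.78 | 5.43 | 6.47 | 4.09 |
| 20 (0) | 4.81 | 4.81 | 7.22 | 4.44 |
| 20 (4) | 5.24 | 4.77 | 7.60 | 3.96 |

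Repeat runs with 88 completers gave 5.0–6.0% with 5 candidates, 6.2–6.4% with 10 and 7.2–8.2% with 20, against 4.4–5.1% for the fixed model. Over both sets:

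- 5 candidates: excess 0 to 1 point.
- 10 candidates: 1 to 2 points (5.96 − 5 = 1.0; 6.47 − 4.78 = 1.7 against the fixed model in the same runs).
- 20 candidates: 2 to 4 points (7.2 − 5 = 2.2; at most 8.2 − 4.4 = 3.8, highest selected rate against lowest fixed rate).

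The last column stays at 4.0–4.9%, so the imbalance rule alone does not inflate.

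**3. Leaving out the strata.** 8,000 trials per cell, six centres by two hours groups, blocks of four (my assumption), no treatment effect. Stratum-effect SDs are in residual-SD units. Entries are % rejected.

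| Stratum-effect SD | n = 88: omitted / kept | n = 118: omitted / kept |
|---|---|---|
| 0 | 4.9 / 4.8 | 5.0 / 5.1 |
| 0.2 | 4.3 / 4.8 | 4.5 / 5.0 |
| 0.4 | 3.7 / 5.2 | 3.6 / 5.1 |
| 0.6 | 2.7 / 5.3 | 2.3 / 4.9 |

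Omitting prognostic strata makes the test conservative; keeping them holds it near 5%.

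**4. What the strata could gain.** Power = Φ(15 / √(2825 × 0.4375 × (1 − R²) / 44) − 1.96), where R² is the share of residual variance that the strata explain (an assumption).

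- R² = 0: 15 / 5.30 − 1.96 = 0.87, power 81%.
- R² = 0.05: 15 / 5.17 − 1.96 = 0.94, power 83%.
- R² = 0.10: 15 / 5.03 − 1.96 = 1.02, power 85%.

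**The case against.** The best defence is that the wording is conditional. Covariates are adjusted for only potentially and where applicable, and selection happens only when required. Backward selection is a general default for every analysis in Table 2. A separate analysis plan may hold a short, named list, and with five candidates the inflation is at most about a point. This stands as a limit on size: the article allows the inflation but does not make it certain. It does not remove the point. The article states the selection rule and defends it as conservative, and a list of candidates would still be thinned on outcome data if the rule were followed.

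A reader might infer three stronger things that the documents do not support.

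- **That the strata are dropped from the model.** The article does not say so, and listing them is commonly left to the analysis plan. If they were dropped, the error would fall, not rise.
- **That imbalance alone admits a covariate.** The definition of a confounder requires both relation to outcome and imbalance, and that rule did not inflate the error.
- **That the analyst may report the best of several models.** Taking the smallest p-value among the baseline-only, backward-selected and imbalance-adjusted models would give 5.8–10.2% in the same simulations. Nothing in the article says that this will be done, so it is only an upper bound on what the loose wording permits.

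**Conclusion.** The point holds in a limited form. The article lets outcome data decide the primary model beyond baseline LVMI and does not account for this in the 5% test. Its assurance about the 10% rule is wrong for backward selection, where the error can exceed 5% by the amounts shown above. To call the primary test invalid would go too far: the excess is small with a short candidate list and depends on a list that the article does not give. The simulations also assume independent normal covariates. They measured rejection rates, so they speak to the claim of conservatism and not to bias in the estimate. The sample size is unaffected.

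**What to change.** For the primary endpoint:

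- Prespecify the model as 12-month LVMI on arm, baseline LVMI, treating centre and hours stratum (≤18 versus >18 hours per week), with a rule stated in advance for small centres.
- Remove the 10% threshold, backward selection and imbalance-triggered adjustment.
- Name any further prognostic covariate before allocation and MRI data are merged.
- Report data-selected models only as labelled sensitivity analyses.
- Delete the clause that presents the 10% rule as unbiased and conservative.

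The cost is wording plus the stratum terms. With 88 completers, the intercept, arm and baseline leave 88 − 3 = 85 degrees of freedom; five centre terms and one hours term take 6, leaving 79. Enrolment stays at 118. If the strata are prognostic, the change gains some precision.
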